## Abstract

**Introduction::**

Myopia is the most common cause of avoidable visual impairment worldwide, which causes huge economic burden and social burden. There are several ways to treat and reduce myopia, but all have drawbacks; this reality drives us to search for additional effective and low-risk interventions of treatment for myopia. Acupuncture is an ancient therapy with a history of thousands of years and is now widely used in the medical system. Some randomized controlled trials have reported that acupuncture, as an adjuvant therapy, can effectively improve the diopter and vision in the sense of myopic children. Deqi is a long-standing belief to ensure the efficacy of acupuncture in the treatment of myopia, but this belief has not been confirmed by sufficient evidence of randomized controlled trials.

**Methods::**

This clinical study is a parallel-group, randomized controlled, and single blind study. Three hundred eligible adolescents will randomly be divided into acupuncture Deqi group, acupuncture without Deqi group, and waiting list group. All groups will be given frame glasses for corrective treatment; patients in the acupuncture Deqi group will be treated with acupuncture at acupoints around the eyes and flat puncture to Deqi, while acupuncture without Deqi group will not flat puncture to Deqi. The waiting list group will not receive acupuncture treatment. The primary outcome will be diopter measurement. Adverse events and safety indexes will be recorded throughout the study.

**Discussion::**

Our study will compare acupuncture Deqi with acupuncture without Deqi, and place it in a control group for the treatment of myopia. The results of this trial are expected to provide solid evidence for the effectiveness and safety of acupuncture combined with Deqi in the treatment of myopia, and hope to provide a reference for clinical practice. The primary outcome will be diopter measurement of the patients before treatment.

**Trial registration::**

ChiCTR2000037874, registered September 3, 2020.

## Introduction

1

Myopia is the most common cause of avoidable visual impairment worldwide.^[1,2]^ Young academics in South-East Asia now face a frequency of up to 95.5% of myopia,^[3]^ accompanied by a high prevalence of high myopia (10–20%).^[4]^ In 2000, there were 1406 million myopia patients and 163 million high myopia patients, and it is predicted that by 2050, there will be 4758 million myopia patients (49.8% of the world population).^[5]^ Myopia brings further vision challenges, as high myopia increases the risk of pathologic ocular changes such as cataract, glaucoma, retinal detachment, myopic macular degeneration, and myopic choroidal neovascularization, all of which can cause irreversible vision loss.^[6,7]^ The global potential productivity loss associated with the burden of vision impairment was estimated at US$244 billion from uncorrected myopia and US$6 billion from myopic macular degeneration.^[8]^

The multifactorial mechanism of the increased prevalence of myopia is not fully understood. Several theories have been proposed to explain the recent increase and its earlier onset in children, including genetic markers,^[9,10]^ increased near work,^[11]^ and less time spent outdoors.^[12,13]^ There has been an increase in efforts to slow the progression of myopia, and a variety of treatment methods have been recommended for the management of myopia. Conventional therapies included single vision spectacle lenses, multifocal eyeglasses, novel lens eyeglasses, various contact lens therapies, orthokeratology, and muscarinic antagonists such as atropine and pirenzepine.^[14,15]^ However, it is reported that none of the spectacle lenses had any significant effect in slowing the progression of myopia. Gas permeable contact lenses have been shown to slow the progression of myopia, but the low incidence of microbial keratitis should not be dismissed, especially in children. The pharmacological treatment has been reported to be associated with adverse effects, including pupil dilation and temporary paralysis of accommodation.^[16–19]^ Consequently, this reality drives us to search for additional effective and low-risk interventions of treatment for myopia.

Acupuncture is an ancient therapy with a history of thousands of years and is now widely used in the medical system. Some clinical studies and systematic reviews show that acupuncture is increasingly used in the clinical treatment of many eye diseases, including dry eye syndrome,^[20]^ blepharoptosis,^[21]^ oculomotor paralysis,^[22]^ blepharospasm,^[23]^ and other ophthalmic diseases, and has a good effect.^[24,25]^ In addition, some randomized controlled trials (RCTs) have reported that acupuncture, as an adjuvant therapy, can effectively improve the diopter and vision in the sense of myopic children.^[26,27]^ Deqi is considered to be an important parameter to achieve curative effect in acupuncture treatment in traditional Chinese medicine theory and practice.^[28]^ Deqi is a complex cluster of sensation evoked by acupuncture stimulation, including aching, dull, heavy, numb, radiating, spreading, and tingling.^[29]^ Modern neuroimaging monitors the dynamic response of acupuncture with specific regions to the whole brain.^[30–33]^ Compared with sham acupuncture, verum acupuncture at true acupuncture points is more likely to elicit a sense of de qi, and the acupuncture needle sensations of Deqi and sharp pain are associated with different patterns of activations and deactivations in the brain.^[34,35]^ The concept of Deqi is a long-standing belief to ensure the efficacy of acupuncture in the treatment of myopia, but this belief has not been confirmed by sufficient evidence of RCTs. In the current paper, we designed a randomized, single-blind, large-scale clinical trial to compare the curative effect of acupuncture for Deqi and acupuncture without Deqi in adolescent patients with myopia.

## Methods/Design

2

### Ethics and dissemination

2.1

The protocols to be used adhere to the principles of the Declaration of Helsinki and have been approved by Chinese Clinical Trial Registry (ChiCTR2000037874). Also, the trial reported in this article is registered by the Chinese Clinical Trial Registry with an identifier of ChiECRCT20200196. Written informed consent will be obtained from each participant before any treatment is given.

### Study design

2.2

This clinical study is a parallel-group, randomized controlled, and single-blind study. The experiment will begin in August 2020 and will be completed in August 2023. After obtaining informed consent, 300 eligible adolescents will be recruited and randomly divided into acupuncture Deqi group, acupuncture without Deqi group, and waiting list group. The trial will include a 3-month treatment period and a 9-month follow-up period. All groups will be given frame glasses for corrective treatment; patients in the acupuncture Deqi group will also be treated with acupuncture at acupoints around the eyes to Deqi, while acupuncture without Deqi group will be treated with acupuncture, but no needle manipulation will be performed. The waiting list group will not receive acupuncture treatment. Results will be assessed at 3 points, including baseline, end of acupuncture treatment, and end of follow-up (Fig. 1 flowchart and Fig. 2 visit indicators). The purpose of this study is to objectively evaluate the clinical efficacy of acupuncture at 3 acupoints (Sizhukong, Tongziliao, and Sibai) in adolescents with myopia. All patients will be required to complete written informed consent before enrolment. If patients are unable to complete written informed consent, it will be obtained from their relatives.

**Figure 1 F1:**
[figure not shown]
Spirit figure of enrollment, interventions, and assessments. Basic treatment: Conventional frame glasses correction treatment and health education; Safety index: Blood, urine, routine stool, liver function (ALT, AST), renal function (BUN, SCr), and electrocardiogram.

**Figure 2 F2:**
[figure not shown]
Flowchart of the study design.

### Recruitment strategies

2.3

The trial will take place at the Teaching Hospital of Chengdu University of Traditional Chinese Medicine (TCM), China. Through flyers and social media advertisements, participants with myopia will be recruited from the Elementary School near the Chengdu University of Traditional Chinese Medicine. The subjects will be informed of the details regarding the trial plan and those who voluntarily participate in the trial will receive free ophthalmologic examinations. All participants or their guardians have the right to participate or drop out at any time, and will be required to sign the informed written consent before any study procedures.

### Diagnostic criteria

2.4

IMI's descriptive (qualitative) definition and quantitative definition of myopia are summarized in Table 1.^[36]^

**Table 1 T1:**
[figure not shown]
IMI's proposed qualitative definition and quantitative threshold for myopia.

### Diagnostic criteria of TCM syndrome classification

2.5

Refer to the 2012 editions of *Diagnosis and Efficacy Standards for Diseases and Syndromes of Traditional Chinese Medicine*^[37]^ and *Chinese Medicine Ophthalmology*^[38]^ on the diagnostic basis of “being near and far away,” and combined with clinical practice.

Diagnostic criteria: (liver and kidney deficiency, spleen deficiency syndrome)

Main symptoms: blurred vision, clear vision near;

Secondary symptoms: eye intolerance, dryness and discomfort, distension and pain, photophobia; fatigue, less food, palpitations and forgetfulness, waist and knee acid soft, dizziness tinnitus;

Coating on the tongue: light coating on the tongue;

Pulse: thin or weak; pulse.

This syndrome can be diagnosed by combining the lingual vein with 3 or more secondary symptoms.

### Inclusion criteria

2.6

Patients with myopia who meet the following inclusion criteria will be enrolled in the trial:

(1)Age of 7∼16 years;(2)Meet the diagnostic criteria of myopia;(3)Agree to sign an informed consent form and volunteer for the research.

### Exclusion criteria

2.7

Patients meeting any of the following criteria will be excluded from the study:

(1)Patients age <7 years or >16 years, patients not suffering from myopia, or patients with myopia and strabismus/amblyopia;(2)myopia related to retinal dystrophies or collagen syndromes, and developmental disorders;(3)subjects with serious systemic diseases, such as cerebrovascular, liver, kidney, hematopoietic system, and psychiatric diseases;(4)use other related drugs or treatments within 2 weeks;(5)Spherical equivalent (SE) < -0.5D, or combined with pathologic myopia-related fundus changes and/or significant visual function impairment;(6)the affected eyes have other diseases that affect the determination of acupuncture efficacy;(7)patients with less than 14 weeks of follow-up, inability to obtain refraction data in the first 14 weeks, patients lost to follow-up, or unable to keep office follow-up at our institution.

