### Sample size

2.9

This study is a RCT, and the diopter of the research object is the main observed outcome index. According to previous literature reports, it is estimated that the mean diopter of experimental group 1 is -1.52, the standard deviation is 0.87, and the diopter of experimental group 2 is- 1.81, the standard deviation is 1.25. Set α = 0.25 (2-sided) and β = 0.10. We use PASS 15 software (PASS 15.0.5 NCSS, LLC USA) to calculate the experimental size of the test group and the control group N1 = N2 = N3 = 74 cases. Assuming that the loss to follow-up rate of the study subjects is 20%, the sample size is N1 = N2 =  = N3 = 74÷0.8 = 93 cases. Therefore, the minimum sample size included in this study is 279 cases. In the actual study, a total of 300 cases will be included.

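### Exclusion criterion 5, as printed, removes children more myopic than -0.5 D and so contradicts the trial's own myopia requirement and planning means

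*Protocol article*

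**What the plan says.** Four places in the Protocol article bear on who may enter.

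- Section 2.6, inclusion criterion 2: "Meet the diagnostic criteria of myopia". Section 2.4 takes the definition from Table 1, captioned "IMI's proposed qualitative definition and quantitative threshold for myopia". The content of that table is not visible in the text available for review.
- Section 2.7, opening line: "Patients meeting any of the following criteria will be excluded from the study". One criterion is enough to exclude.
- Section 2.7, exclusion criterion 1, removes "patients not suffering from myopia, or patients with myopia and strabismus/amblyopia".
- Section 2.7, exclusion criterion 5, reads "Spherical equivalent (SE) < -0.5D, or combined with pathologic myopia-related fundus changes", and then adds marked impairment of visual function as a further condition.

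Section 2.9 fixes the sign convention. It says "it is estimated that the mean diopter of experimental group 1 is -1.52", with SD 0.87, and gives -1.81 with SD 1.25 for the second group. Myopic refraction is thus written as a negative number.

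**The concern.** On the signed scale, a value below -0.5 D is more myopic than -0.5 D. Read as printed, criterion 5 turns away the children whom inclusion criterion 2 asks for, while exclusion criterion 1 turns away those without myopia. The two planning means lie on the excluded side of the threshold.

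Diopter is the primary outcome (section 2.12.5), so the eligible SE range defines the population to which the result applies. A site that follows the text exactly cannot recruit the children the trial is planned around. A site that ignores or reinterprets it enrols children who formally meet an exclusion criterion. Section 2.16 limits the per-protocol set to completers without significant protocol violations, so the contradiction could reach the analysis as well as recruitment.

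**Working it through.** The protocol states no figure on this point, so there is nothing to reproduce. The check is first logical, then a rough sizing.

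**Logic**

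1. Any single exclusion criterion suffices (section 2.7).
2. In criterion 5 the SE condition is joined by *or* to the fundus and visual-function conditions, so it excludes on its own.
3. Section 2.9 uses negative diopters for myopia. Hence SE < -0.5 D covers, for example, -1.0, -1.52 and -1.81 D.
4. Inclusion criterion 2 requires myopia and exclusion criterion 1 removes its absence. What can remain is at most a narrow band of myopic children at or just above -0.5 D. Whether that band holds anyone depends on the Table 1 cut-off, which is not visible.
5. Nothing in the available text reverses or qualifies the sign.

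**Illustrative size**

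Inputs from section 2.9: mean -1.52, SD 0.87 (group 1); mean -1.81, SD 1.25 (group 2). Assumptions that are not in the protocol: these values describe baseline SE, and SE is normally distributed.

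Share excluded = Φ((-0.5 - mean)/SD)

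- Group 1: Φ((-0.5 + 1.52)/0.87) = Φ(1.172) = 0.879
- Group 2: Φ((-0.5 + 1.81)/1.25) = Φ(1.048) = 0.853

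The share left is 1 - 0.879 = 0.121 and 1 - 0.853 = 0.147. It splits at 0 D as follows:

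| | Between -0.5 and 0 D | At or above 0 D |
|---|---|---|
| Group 1 | 0.960 - 0.879 ≈ 0.080 | 1 - 0.960 = 0.040 |
| Group 2 | 0.926 - 0.853 ≈ 0.074 | 1 - 0.926 = 0.074 |

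Here 0.960 = Φ(1.52/0.87) and 0.926 = Φ(1.81/1.25). Splits are computed before rounding.

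**If the planning values are outcome rather than entry values**

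Children who entered at -0.5 D or above would have to move, on average, by at least 1.52 - 0.5 = 1.02 D (group 1) or 1.81 - 0.5 = 1.31 D (group 2) in the myopic direction, within a 12-month study, to reach those means. That is a large shift to assume, and the protocol does not state that it assumes one. The tension with section 2.9 therefore does not disappear under this reading.

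**The case against.** The best defence is that this is a slip of the pen. The aim, the recruitment text, inclusion criterion 2 and exclusion criterion 1 all concern children with myopia, and criterion 5 agrees with them if read as less than half a diopter of myopia. The article has other typographical slips, such as a month name where a follow-up month is meant in section 2.13. A slip is plausible, but that does not cure the printed rule. A second repair is also possible: the same sentence goes on to pathologic fundus changes, so a severity limit with a wrong value could have been meant. The two repairs cut off opposite ends of the refraction range, and the text does not settle which applies.

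The objection does succeed on size. Section 2.9 does not call its means baseline values. They differ between arms, which randomised groups would not be expected to do at entry, so they may be anticipated outcomes. Normality is also doubtful, since it puts 4 to 7% at or above 0 D in a trial restricted to myopia.

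Four stronger readings are tempting and are not supported:

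- *The children left over are mostly non-myopic.* By sign alone, about 8 of the 12 percentage points in group 1, and about half in group 2, are still negative. Classifying them needs the Table 1 cut-off.
- *The planning means cannot occur.* The criterion restricts entry only, and section 2.9 does not say when its means apply. Implausible is as far as the text goes.
- *Every enrolled child would be a protocol violator.* A child at or above -0.5 D does not breach this condition. Moreover, only significant violations remove a child from the per-protocol set, and the full analysis set keeps everyone randomised.
- *The investigators chose to enrol children without myopia.* Nothing in the protocol suggests this.

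**Conclusion.** The contradiction stands. As printed, exclusion criterion 5 conflicts with inclusion criterion 2, exclusion criterion 1 and the planning means in section 2.9. This rests on the wording and the sign convention alone, and needs neither Table 1 nor any distributional assumption.

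Applied literally, the rule removes most of the target population. The figure of about 85 to 88% is illustrative: it holds only if baseline SE is normal with the section 2.9 means and SDs. If sites disregard the rule, typical enrolled children with SE below -0.5 D breach an exclusion criterion, and they might be dropped from the per-protocol set if that breach is judged significant. How many eligible children a literal reading would leave cannot be determined without the Table 1 threshold.

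This is an eligibility rule that is wrong as written, and it needs correction before it is relied on.

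**What to change.** Reconcile criterion 5 with the myopia definition in Table 1, inclusion criterion 2, exclusion criterion 1 and section 2.9. The sponsor should state which of two things was meant: an entry threshold whose inequality is reversed, or a severity limit whose value is wrong. It should then give the eligible SE range once, with its sign. The choice of value belongs to the sponsor. If children have already been enrolled under a working interpretation, record which one was used, so that the per-protocol set is not decided by the printed text.

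Cost: a one-line eligibility amendment.

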### Informed consent

2.8

Before the study, the general study process and the responsibilities of the participants and researchers will be explained to potential participants or their guardians. Participants or their guardians will be informed that their entry into the trial is entirely voluntary and that they could withdraw at any time. In the event of their withdrawal, data collected on the participant will not be erased and will be used in the final analyses. Written informed consent should be obtained from each participant before he or she undergoes any interventions related to the study.

### Sample size

2.9

This study is a RCT, and the diopter of the research object is the main observed outcome index. According to previous literature reports, it is estimated that the mean diopter of experimental group 1 is -1.52, the standard deviation is 0.87, and the diopter of experimental group 2 is- 1.81, the standard deviation is 1.25. Set α = 0.25 (2-sided) and β = 0.10. We use PASS 15 software (PASS 15.0.5 NCSS, LLC USA) to calculate the experimental size of the test group and the control group N1 = N2 = N3 = 74 cases. Assuming that the loss to follow-up rate of the study subjects is 20%, the sample size is N1 = N2 =  = N3 = 74÷0.8 = 93 cases. Therefore, the minimum sample size included in this study is 279 cases. In the actual study, a total of 300 cases will be included.

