### Randomization and allocation concealment

2.10

Central random system is used to realize random grouping and random hiding of hierarchical blocks. This study is stratified according to the subcenter, randomly divided into acupuncture Deqi group, acupuncture without Deqi group, and waiting list group at a ratio of 1:1:1. A statistician from Sichuan Evidence-based Medicine Center of Traditional Chinese Medicine will use SAS 9.2 software (SAS, Cary, NC) to generate random sequences in 3 rounds of random sentences, list the random code tables corresponding to the serial numbers 001–300, and generate treatment assignments for 300 subjects. This process is implemented by the online central random system. The researcher enters the screening information of the prospective subjects on the central random system and obtains the subject number. After meeting the subject's criteria and signing the informed consent form, they are randomly divided into groups, and the random number is generated. Examiners and researchers cannot foresee the grouping information of the subjects, and the random number is managed by Sichuan Evidence-based Medicine Center of Traditional Chinese Medicine. Until the end of the study, the subjects, clinicians, and outcome measurers did not know the grouping of subjects.

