### Statistical analyses

2.16

Data analyses will be processed with SPSS 22.0 (SPSS Inc., Chicago, IL) and supervised by a skilled statistician blinded to group allocation.

The Full Analysis Set (FAS) is for all participants who have been randomized in terms of the intention-to-treat (ITT), and the per-protocol analysis set (PPS) and is for the individuals who complete the trial and do not have significant protocol violations. On the basis of rule of the last-observation-carried-forward, missing values will be imputed. In order to evaluate therapeutic effect and safety, the FAS and PPS will be used simultaneously.

Categorical data, such as gender and medical history, will be tabulated with frequencies or percentages; and continuous data, such as age and disease course, will be reported as mean ± standard deviation (SD), or median. For the baseline variables, sociodemographic data and other basic indicators will be carried out using analysis of variance (ANOVA) and χ^2^. To compare variables before and after treatment in the same group, a paired *t* test will be used. Repeated-measures ANOVA will be used to compare the intergroup differences among the 3 groups. Tests of ITT between the acupuncture with the deqi group and acupuncture without the deqi group arms and between the acupuncture withou the deqi group and waiting-list group arms with respect to the change will based on time-intervention interactions in the mixed-effect models. A *P* value of less than .05 (2-sided) indicates a statistically significant difference, with 95% confidence intervals.

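### The 74 per arm in section 2.9 does not follow from its own inputs, and its alpha of 0.25 contradicts the .05 used for analysis, so the stated 90% power is unsupported

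*Protocol article*

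**What the plan says.** Section 2.9 (Sample size) names diopter as the main outcome and gives two sets of planning values. The first reads "the mean diopter of experimental group 1 is -1.52, the standard deviation is 0.87"; the corresponding mean and SD for the other group are -1.81 and 1.25. It then says "Set α = 0.25 (2-sided) and β = 0.10", and uses PASS 15 to "calculate the experimental size of the test group and the control group N1 = N2 = N3 = 74 cases". The allowance for loss follows ("Assuming that the loss to follow-up rate of the study subjects is 20"%), which takes 74 to 93 per arm and 279 in total; 300 are to be enrolled. Section 2.10 allocates the three arms 1:1:1, so 300 means 100 per arm.

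Section 2.16 (Statistical analyses) uses a different threshold: a P "value of less than .05 (2-sided) indicates a statistically significant difference". It tests Deqi against no Deqi, and no Deqi against waiting list, on change, through time-by-intervention interactions in mixed-effect models. The full analysis set is everyone randomised, with missing values filled by last observation carried forward.

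**The concern.** Two things are wrong on the page. The sample size is not the answer to the calculation described, and the error rate in that calculation is five times the one used to judge the result. An alpha of 0.25 looks like a misprint, but correcting it downwards raises the required size and moves it further from 74.

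The 90% power is what justifies enrolling 300 children and adolescents. If it is unsupported, a non-significant Deqi comparison could be read as evidence that Deqi adds nothing, when nobody has shown that the trial was likely to detect its own planning difference.

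**Working it through.** **Inputs (section 2.9).** Difference: 1.81 - 1.52 = 0.29 D. Sum of variances: 0.87² + 1.25² = 0.7569 + 1.5625 = 2.3194. Power 90%, so z = 1.282. Equal allocation.

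**The plan's own chain.** 74 / 0.8 = 92.5, rounded up to 93, and 93 × 3 = 279. These steps are right. The fault lies in the 74.

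**Size per arm.** n = (z_alpha + z_beta)² × 2.3194 / 0.29² = (z_alpha + z_beta)² × 27.58.

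| Alpha | z_alpha | n per arm |
|---|---|---|
| 0.25 two-sided (as printed) | 1.150 | 163.1, so 164 |
| 0.05 two-sided (section 2.16) | 1.960 | 290 |
| 0.025 two-sided | 2.241 | 343 |
| 0.25 one-sided | 0.674 | 106 |

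Using only the smaller SD of 0.87 in both groups still gives 107 at two-sided 0.25 and 190 at two-sided 0.05. Solving for the two-sided alpha at which 74 per arm has 90% power returns 0.72. A few combinations come near 74, such as 80% power with an SD of 0.87 in both groups at two-sided 0.25, which gives 72, but that one contradicts the stated beta and SDs.

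**Power on raw diopter at one visit, for 0.29 D.** Power = Φ(0.29 / √(2.3194/n) - z_alpha). At two-sided 0.05:

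- 74 per arm: 0.29 / 0.1770 = 1.638; Φ(-0.322) = 37%.
- 80 per arm (100 less 20% loss): 0.29 / 0.1703 = 1.703; Φ(-0.257) = 40%.
- 100 per arm (all randomised): 0.29 / 0.1523 = 1.904; Φ(-0.056) = 48%.

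The unequal-variance t calculation agrees within half a percentage point. At the printed two-sided 0.25, 74 per arm gives Φ(1.638 - 1.150) = 69%. At two-sided 0.025, 80 per arm gives about 30%.

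**Detectable difference with 80 per arm at two-sided 0.05.** For 90% power, 3.242 × 0.1703 = 0.55 D; for 80% power, 2.802 × 0.1703 = 0.48 D.

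**Power for change.** The article gives no correlation r between baseline and follow-up. Assume a simple change score, SDs constant over time, the same 0.29 D, 80 per arm and two-sided 0.05. The variance sum becomes 2(1 - r) × 2.3194.

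| Assumed r | Power |
|---|---|
| 0.5 | 40% |
| 0.7 | 59% |
| 0.8 | 77% |
| 0.86 | 90% |
| 0.9 | 97% |

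With adjustment for baseline instead, the required size is multiplied by (1 - r²). Bringing 290 down to 74 would need r = √(1 - 74/290) = 0.86.

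**The case against.** The strongest reply concerns the analysis. The 40% belongs to a single-visit comparison of diopter level, whereas section 2.16 tests change in a mixed model, with diopter measured at baseline and six later visits (section 2.12.5). Serial refraction in the same eyes may be strongly correlated, and then power could be far higher. This stands. A reader might infer that the trial really has about 40% power, or less than an even chance of detecting its planned difference; the document does not support that as an unconditional statement. Nor does the reply rescue the 90%, because section 2.9 works from raw means and SDs and states no correlation.

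Second, 80 per arm is the lower case. The full analysis set with carried-forward values keeps all 100, for which the raw-diopter figure is 48%. This also stands, and both figures should be given.

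Third, three equal sizes could come from a three-group calculation whose third mean was left out. A one-way ANOVA at 0.05 with a common SD of 1.077 and a third mean near -2.15 does give 90% power at 74 per arm. But that mean was found by solving backwards and is nowhere in the article, and such a calculation would not power the pairwise tests in section 2.16. It is a reason to ask for the PASS inputs; it does not make the section correct as printed.

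Fourth, 0.25 might be a misprint for 0.025, a split of 0.05 over the two pairwise tests. That is possible, so 0.05 should not be presumed to be what the authors meant in section 2.9. It would raise the required size to 343, and section 2.16 mentions no such split.

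Finally, section 2.9 speaks only of experimental groups 1 and 2. Reading these as Deqi and no Deqi is natural but is an inference.

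**Conclusion.** The point holds as an error in the stated calculation. From the printed inputs, 90% power needs 164, 290 or 343 per arm at two-sided 0.25, 0.05 or 0.025, against the 74 reported; the 93 and 279 inherit the error. Sections 2.9 and 2.16 give conflicting alphas. These findings rest only on the article's own figures and the standard two-sample formula.

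The power actually available is a conditional matter. On raw diopter at one visit and two-sided 0.05 it is 40% to 48% for 0.29 D, depending on whether 80 or 100 per arm count. For change with 80 per arm it runs from about 40% to over 90% across assumed correlations of 0.5 to 0.9. The conclusion is that 90% is unsupported, not that any single lower figure is the trial's true power.

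**What to change.** 1. **Reconcile alpha between sections 2.9 and 2.16.** Use two-sided 0.05 as in section 2.16, unless a multiplicity-adjusted 0.025 was intended; in that case state it in both sections, with the comparisons it covers.
2. **Replace 74, 93 and 279 with a reproducible calculation.** Recover the PASS inputs first. State the comparison, the test, the means and SDs, any third-group mean, any correlation, alpha, power and loss.
3. **State what 300 participants deliver,** in one of two ways:
   - on raw diopter at two-sided 0.05: about 40% to 48% power for 0.29 D or, with 80 evaluable per arm, a detectable difference of about 0.48 D at 80% power and 0.55 D at 90%;
   - for the change or baseline-adjusted analysis: the power with its assumed correlation or residual SD, and a range around that assumption.

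The cost is a rewrite of section 2.9, and of the threshold sentence in section 2.16 if 0.025 was meant. No additional patients are required. The stated power may become less favourable.
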